### Methods for additional analyses (e.g. subgroup analyses) {20b}

Differential treatment effects will be analyzed by including interaction terms for subgroups by intervention group. Prespecified subgroups include tumor grade (low-grade glioma vs. high-grade glioma), number of risk factors [13] fulfilled (1 or 2), duration of intervention (sham or rnTMS training, median split), surgeons, and tumor volume. Parallel to interaction effects estimated marginal treatment effects of the subgroups and 95% CI will be reported. Descriptive measures, effect estimates, and 95% confidence intervals will be calculated for each primary and secondary analysis.

Sensitivity analyses include per-protocol analyses and complete case analyses.

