### Intervention description {11a}

Participants in the intervention arm will receive rnTMS over the affected motor cortex using a Nexstim NBS 5 stimulator with neuronavigation (Nexstim, Helsinki, Finland) followed by a short motor training. The stimulation target is selected by combining TMS with tractography. Functional fibers of the corticospinal tract closest to the tumor and hence, most endangered by resection of the tumor, are identified. RnTMS will be centered over the cortical endings of those fibers. Stimulation is applied at 1 Hz [14] and an intensity of 110% [10]. The duration of the intervention is 30 min per session twice daily (90 min apart) over multiple days to maximize the treatment dose in the short preoperative time [9]. The individual study duration depends on the time available before surgery (≥ 5 days, maximum 28 days). While we assume that longer trial durations will maximize the effects and clinical impact of the stimulation [8, 15], the effects of rnTMS have already been shown after a single session [16]. A short motor training of 10 min will be applied after rnTMS stimulation to facilitate the recruitment of additional networks for motor function while motor fibers in danger during surgery are temporarily inhibited [7]. A set of exercises has been established together with physiotherapists, allowing adaption of the training based on participants’ abilities. See also {13} for a detailed description of the participant timeline and procedures performed at each timepoint.

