#### GTR

Until today there are no studies analyzing the GTR in rnTMS compared to sham, but only studies with nTMS. Picht et al. [25] demonstrated a GTR of 61% in the intervention group versus 45% in the control group (OR 1.91). We expect a higher difference in our groups due to the induction of plasticity in this intervention. We expect an OR of 2.85 or higher (for example for proportions of 74% vs. 50% of GTR in the intervention vs. control group). Using information of 66 sham and 66 rnTMS patients it will be possible to demonstrate such a difference using a chi-square test (power=82%, two-sided significance level of 0.05) (nQuery Advisor 8). The statistical analysis will be done using binary logistic regression accounting for the center and age group. Using this analysis strategy will result in at least the same or higher power.

Both primary hypotheses will be tested hierarchically at a two-sided significance level of 0.05. To account for possible dropouts (approximately 10%), 148 patients in total will be included in the study to ensure at least 132 complete cases, even if we apply missing value imputation methods using 30 complete data sets (if missing at random (MAR) or missing completely at random (MCAR) assumption holds). To evaluate if individual missings are MAR, MCAR, or missing not at random (MNAR) we will use information on reasons of missings or dropouts (e.g. if patients drop out due to worsening of health status or not). In case of premature death (before measuring the primary outcome, the BMRC score for those patients will be set to the worst possible value.

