#### Description of the primary efficacy analysis and population

(1) Non-inferiority of motor status at T3 in the rnTMS group vs. sham group will be tested using an ordinal regression model (adjusted for baseline motor status) with dependent variable motor status at T3 (ordinal: six categories). Additionally, center, duration of rnTMS/sham training, and age will be included as covariates. Non-inferiority is successfully proven, if the upper limit of the 95% CI of the odds ratio for a worse outcome in the intervention group is below 1.35 according to the pre-specified non-inferiority margin. (2) The second main hypothesis, that the GTR is higher in the rnTMS compared to the sham group, will be tested (only if the first hypothesis has been proven, hierarchical testing) at a two-sided significance level of *α* = 0.05 using a binary logistic regression model with gross total resection (yes/no) as a dependent variable, group allocation, center, duration of rnTMS/sham training, and age as independent variables. A per-protocol analysis will be conducted as a sensitivity analysis.

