## Discussion

The PRECON study is an exploratory phase 2b clinical trial in patients with motor-eloquent brain tumors, aiming to show the efficacy of rnTMS to facilitate the tumor-induced functional reorganization of motor areas. We hypothesize that this reorganization leads to a better or comparable motor function 3 months postoperatively and a higher rate of gross total resections in the intervention group compared to sham stimulation. Based on this exploratory trial it will be possible to get more robust effect estimates for the outcomes and analyze the safety profile of the intervention to proceed to a confirmatory trial. In a larger confirmatory trial, it would also be possible to analyze different secondary endpoints more thoroughly and potential differential treatment effects in subgroups with more power.

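### Effect modification by intervention duration is tested only with duration cut at the sample median, which wastes information if the effect grows with duration

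*Protocol article*

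**What the plan says.** Intervention length differs between patients. Under Intervention description {11a}: "The individual study duration depends on the time available before surgery (≥ 5 days, maximum 28 days". The same section states an expectation about its effect: "While we assume that longer trial durations will maximize the effects and clinical impact of the stimulation".

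The additional analyses {20b} say how effect modification is tested: "Differential treatment effects will be analyzed by including interaction terms for subgroups by intervention group". Duration is one of five listed subgroup variables, with its coding given: "duration of intervention (sham or rnTMS training, median split". Marginal effects with 95% CIs are to be reported for the subgroups.

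Duration also enters both primary models. For GTR the model has "group allocation, center, duration of rnTMS/sham training, and age as independent variables"; the ordinal model for motor status includes it as well. No split is stated there, and in both it is a main effect only.

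The Discussion calls the trial exploratory and gives its purpose: "Based on this exploratory trial it will be possible to get more robust effect estimates for the outcomes". It leaves better-powered subgroup analysis to a larger confirmatory trial.

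**The concern.** A main effect of duration adjusts for differences in outcome between short and long courses. It does not ask whether the treatment effect changes with course length. On the text shown, only the median-split interaction asks that.

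The split treats a 5-day course like one just below the median, and a 28-day course like one just above it. If the effect rises with days, the contrast within each half is thrown away. The cut point is whatever the median turns out to be, so the short and long groups have no fixed meaning outside this sample. A team planning the confirmatory trial would get two estimates tied to that cut, and no estimate at a chosen duration.

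At stake is the yield of one exploratory analysis that bears on an expectation the protocol itself states.

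**Working it through.** **Inputs from the protocol article.** Duration 5–28 days ({11a}); "Using information of 66 sham and 66 rnTMS patients" and "for example for proportions of 74% vs. 50% of GTR" (Sample size, GTR); two-sided α = 0.05. The protocol gives no duration distribution, interaction size or shape, and no power for this interaction. Those are assumptions below, shown as ranges.

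**1. The plan's own figure.** Two-proportion power with mean proportion 0.62:

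Φ{[0.24·√66 − 1.96·√(2·0.62·0.38)] / √(0.74·0.26 + 0.50·0.50)} = Φ{(1.950 − 1.345)/0.665} = Φ(0.91) = 0.818.

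This matches the stated 82%. The odds ratio is (0.74/0.26)/(0.50/0.50) = 2.85, also as stated.

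**2. Information kept by the split.** For a linear trend this is the squared correlation between days and the two-group indicator. With uniform durations on 5, 6, …, 28:

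- variance of days = (24² − 1)/12 = 47.92;
- the halves 5–16 and 17–28 have means 10.5 and 22.5, so between-group variance = (12/2)² = 36;
- information kept = 36/47.92 = 0.751, so 25% is lost.

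The same calculation for other assumed distributions follows. Ranges reflect different parameters and whether patients on the median day go in the lower or upper half.

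| Assumed distribution | Information lost |
|---|---|
| U-shaped | 20% |
| Uniform | 25% |
| Beta(2,2) over the range | 30% |
| Roughly normal around 16.5 days | 34–37% |
| Right-skewed (truncated exponential), scale 10 days | 31–36% |
| Right-skewed, scale 7 days | 39–46% |
| Right-skewed, scale 3–5 days | 41–52% |

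**3. Power of the interaction for GTR.** Logistic models with expected information: 66 per arm, sham GTR 50%, log OR linear in days and equal to ln 2.85 at the mid-range of 16.5 days. If the OR is 1.0 at 5 days, it is 2.85² = 8.1 at 28 days. Power is shown as days / split; the median day is in the lower half.

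| Durations | OR 1.0 to 8.1 | OR 1.91 to 4.25 | OR 0.61 to 13.4 |
|---|---|---|---|
| Uniform | 37% / 29% | 10% / 9% | 63% / 51% |
| Normal (16.5, SD 5) | 20% / 15% | 7% / 7% | 37% / 26% |
| Truncated exponential, scale 7 | 25% / 18% | 8% / 7% | 45% / 32% |
| Truncated exponential, scale 10 | 30% / 22% | 9% / 8% | 53% / 41% |
| Beta(2,4) | 18% / 14% | 7% / 6% | 33% / 25% |

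The first scenario costs about 5–8 points (4 for Beta(2,4)), and up to about 9 for the skewed distributions if patients on the median day go in the upper half. The weak interaction costs about 1 point, and the steep one 9–13.

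Step 2 and step 3 agree. Power of 37% means a noncentrality of 1.96 − 0.34 = 1.62. Multiplying by √0.751 = 0.867 gives 1.40, and Φ(1.40 − 1.96) = 0.29.

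**4. Sensitivity to shape.** In simulation with a threshold at the median (OR 1 below, 8.1 above), the split does better: 67% against 63% with uniform durations, and 66% against 59% with skewed ones. With skewed durations and an effect that saturates at 10 days, the two tie at 35%. With uniform durations and saturation at 14 days, days do better: 30% against 15%.

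**The case against.** The protocol does not call this a dose-response test. Duration is one of five exploratory subgroup variables, and the Discussion concedes that subgroup power is low. A median split is fixed as a rule in advance and balances group sizes. Linearity is not the protocol's assumption: {11a} says only that longer courses should do more, and adds that effects have been seen after a single session. A threshold near the median would favour the split. A detailed SAP is promised before database closure and could add a continuous term.

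Much of this stands. The loss depends on shape, and no figure for it follows from the protocol alone. A reader might infer a firm loss of 14 points or so by assuming right-skewed durations and holding the average OR at 2.85. The documents do not support that. With no effect at 5 days and a mean excess of about 5.5 days, the slope would be 1.047/5.5 = 0.19 per day, and the OR at 28 days would be exp(0.19 × 23), about 80.

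Two parts do not remove the point. Low power is a reason not to give up more of it. And the coding is written into {20b}, so it is a stated choice and not a detail left to the SAP.

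Duration is also set by the time available before surgery. A reader might take a continuous analysis to give a causal effect per day. It would not: differences by duration may reflect urgency or tumour features, and this holds for either coding.

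**Conclusion.** The point holds in a conditional form. For a roughly linear rise in effect, the median split discards about 20–50% of the information on the interaction. With the plan's GTR inputs and an OR rising from 1.0 to 8.1 over 5–28 days, that costs about 5–9 points of power. The cost is about 1 point if the interaction is weak, when power is 10% or less either way; it is larger for steeper slopes and absent for a threshold near the median. These sizes rest on assumed distributions and slopes. Whatever the shape, the cut is sample-dependent, so the subgroup estimates do not carry over to a confirmatory trial.

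A reader might infer that the primary results are compromised. They are not: the split appears only in the subgroup analysis, and neither primary test nor the sample size depends on it. This is a minor improvement to one exploratory analysis.

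**What to change.** In {20b}, replace the median split with a test of the group-by-duration interaction with duration in days, linear, and a prespecified log or restricted cubic spline term as the check on shape. Report the treatment effect with its 95% CI at fixed durations, for example 7, 14 and 21 days, chosen only as reporting points. Keep the median-split estimates as a descriptive display. Add that duration is not randomised, so any difference in effect by duration is exploratory and may reflect urgency or tumour features.

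The cost is about a sentence on the test and one on interpretation, here or in the coming SAP. No new data or patients are needed. The downside is the linearity assumption, which the nonlinearity check covers.

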#### Motor status

Data from a small study by Ille et al. (*n* = 19; [11]) demonstrate high effect sizes of 1.66 for the Fugl-Meyer Assessment (FMA) at 3 months follow up in rnTMS compared to sham (mean change in FMA: 31.9 (standard deviation (SD): 18.4) in rnTMS compared to 4.2 (SD: 10.4) in sham, common SD: 16.7). In a meta-analysis combining 10 study estimates for low-frequency rTMS compared to controls in stroke patients, Hsu et al. [24] reported an effect size of 0.69 (95% CI: 0.42–0.95) regarding motor function outcomes. In our study, we aim to demonstrate non-inferiority of motor status at T3 in the rnTMS group compared to sham using the BMRC score (ordinal values between 0 and 5). We use a non-inferiority margin of 0.5 points (difference of group medians), corresponding to the probability of a worse outcome in the intervention group compared to in the control group of *P*(*x* > *y*) = 55.0% (assuming a mean difference of 0.5 and common standard deviation of 2.5, corresponding to an odds ratio (OR) of 1.35 [15], or Cohen’s *d* of 0.17 [16]). We will show that the OR for a worse outcome in the intervention compared to the sham group is significantly below 1.35 (one-sided significance level *α* = 0.025) using 66 sham patients and 66 rnTMS patients. This is possible if the true OR is at least 0.74 (95% CI: 0.23–1.25) (corresponding to a Mann-Whitney measure of P(x > y) = 45.0%, or Cohen’s *d* of − 0.17). This sample size calculation is based on a simplified dichotomous measure, not an ordinal measure, using a similar effect size for an OR of two proportions (50.0% vs. 42,4%, nQuery Advisor 8): When the sample size is 132 (with group 1 and 2 sample sizes of 66 and 66), a one-sided (upper) 97.5% confidence interval for the odds ratio of two proportions will range from the sample proportion odds ratio of 0.74 to an upper limit of 1.24, assuming a worse outcome in 42.4% of patients in the intervention group and in 50.0% of patients in the control group. The confidence interval was calculated using the Simple Asymptotic Method. While we analyze the primary outcome in an ordinal regression model, we expect a similar effect estimate. We demonstrate this at a one-sided significance level of *α* = 0.025 with a power of 80%. Additionally, in case of a 95% CI of the OR for a worse outcome below 1 in the intervention compared to the control we can demonstrate superiority of the intervention.

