## Statistical methods

### Statistical methods for primary and secondary outcomes {20a}

#### Efficacy

To test both main hypotheses of comparable motor status at T3 and a higher GTR in rnTMS patients compared to sham patients, we will apply hierarchical testing at a two-sided significance level of *α* = 0.05 (Power = 80%). Primary hypotheses will be tested in an intention-to-treat (ITT) framework using multiple imputed datasets in case of missing values (under the assumption of MCAR or MAR) after a single imputation of informative missing values (MNAR) for example for patients with worsened health status or patients who die during follow up.

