### Methods in analysis to handle protocol non-adherence and any statistical methods to handle missing data {20c}

Primary hypotheses will be tested in an ITT framework. The primary population is defined as all randomized patients with a baseline measurement of the primary endpoints. Both primary hypotheses will be tested hierarchically at a two-sided significance level of 0.05. To account for possible dropouts (approximately 10%), 148 patients in total will be included in the study to ensure at least 132 complete cases, even if we apply missing value imputation methods using 30 complete data sets (if MAR or MCAR assumption holds). To evaluate if individual missings are MAR, MCAR, or MNAR we will use information on reasons of missings or dropout (e.g. if patients drop out due to worsening of health status or not). In case of premature death (before measuring the primary outcome), the BMRC score for those patients will be set to the worst possible value.

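### The sensitivity analyses named for the motor-status test do not challenge the missing-at-random assumption for T3 scores not classed as informative

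*Protocol article*

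**What the plan says.** The Efficacy paragraph of section {20a} sets the primary analysis in an ITT framework, "using multiple imputed datasets in case of missing values (under the assumption of MCAR or MAR"). This follows a single imputation of values judged MNAR, with worsened health and death during follow-up as examples. Section {20c} explains the sorting: "To evaluate if individual missings are MAR, MCAR, or MNAR we will use information on reasons of missings or dropout". It adds a rule for deaths: "In case of premature death (before measuring the primary outcome), the BMRC score for those patients will be set to the worst possible value". Thirty imputed data sets are planned.

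The decision rule, in the description of the primary efficacy analysis, is that non-inferiority is shown if the "upper limit of the 95% CI of the odds ratio for a worse outcome in the intervention group is below 1.35". Gross total resection is tested only if that succeeds.

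The robustness checks are in section {20b}: "Sensitivity analyses include per-protocol analyses and complete case analyses". The per-protocol analysis is also named with the primary analysis. Neither analysis set is defined. On the amount of missing data, section {18b} expects about 2% missing BMRC scores at 3 months, while the sample size allows for about 10% dropout.

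**The concern.** The reason-based sorting catches only losses whose recorded reason points to deterioration. A patient lost for an unknown reason, or for one that hides deterioration, goes into the MAR pool. For a non-inferiority claim the dangerous error is that such patients in the rnTMS arm did worse than the model predicts, because that pulls the estimated odds ratio below its true value. No named analysis moves the missing scores in that direction.

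The complete-case analysis looks like a check on the imputation, but for the values treated as MAR it relies on the same assumption. A reader who sees the two results agree may take the claim as robust when that assumption was never varied. Because motor status is the first step of the hierarchy, a fragile result there also opens the test of gross total resection.

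**Working it through.** **Inputs.** From the Motor status part of the sample size section: 66 patients per arm, "assuming a worse outcome in 42.4% of patients in the intervention group and in 50.0% of patients in the control group", and an interval that "will range from the sample proportion odds ratio of 0.74 to an upper limit of 1.24". From section {20c}: 148 randomised, about 10% dropout. From {18b}: about 2% missing. The margin is 1.35. The outcomes of dropouts are assumptions.

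**1. Reproducing the plan's figures.**
- 132 / 0.9 = 146.7, so 147, and 148 for equal arms, or 74 per arm. Ten per cent of 74 is 7.4 (7 to 8 per arm); 2% is 1.5 (1 to 2 per arm).
- OR = (0.424/0.576) / (0.50/0.50) = 0.736.
- SE(log OR) = √(1/27.98 + 1/38.02 + 1/33 + 1/33) = 0.350.
- Upper limit on the OR scale = OR + 1.96 × OR × SE = 0.736 + 1.96 × 0.736 × 0.350 = 1.241. The protocol states 1.24.

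**2. Complete case against MAR imputation.** If only the T3 score is missing and both models use the same covariates, the imputation model is learned from the patients with observed scores, and the draws return the same relation to the analysis. A large simulated example (40,000 patients, six ordered grades, one covariate, true OR 1.35) shows it:

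| Dropout pattern, about 10% per arm | All data | Complete case | MAR imputation |
|---|---|---|---|
| Depends on the covariate only | 1.34 | 1.34 | 1.34 |
| rnTMS losses concentrated in worse grades | 1.34 | 1.11 | 1.11 |

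In the second row both analyses are wrong by the same amount, and they agree.

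**3. How many adverse dropouts matter.** Take 74 per arm and the protocol's two-category simplification. Let *k* rnTMS dropouts all have a worse outcome and leave everyone else at the planning rates. Worse outcomes are then 0.424 × (74 − *k*) + *k* in the rnTMS arm and 37 in the sham arm.

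| *k* | Worse, rnTMS | OR | Upper limit | Below 1.35? |
|---|---|---|---|---|
| 0 (all MAR) | 31.4 | 0.736 | 1.213 | yes |
| 3 | 33.1 | 0.809 | 1.333 | yes |
| 4 | 33.7 | 0.835 | 1.375 | no |
| 8 | 36.0 | 0.947 | 1.557 | no |

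For *k* = 4: OR = 33.68/40.32 = 0.8353; SE = √(1/33.68 + 1/40.32 + 1/37 + 1/37) = 0.3295; upper limit = 0.8353 + 1.96 × 0.8353 × 0.3295 = 1.375.

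A milder version has 8 lost per arm and sham dropouts at 50% worse. rnTMS dropouts at 60% worse give 1.31 (passes); at 75% worse they give 1.40 (fails).

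**4. At 2% missing.** With one or two lost per arm, all rnTMS dropouts worse and sham dropouts at 50%, the limits are 1.25 and 1.29. Only two lost per arm, with both rnTMS patients worse and neither sham patient worse, crosses the margin (1.36).

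**Limits of steps 3 and 4.** Filled-in values are counted as observed, so the limits are slightly too narrow. They also use the planning interval on the OR scale. On the log scale the planned result lies above the margin before any shift (1.46 at 66 per arm, 1.41 at 74). The count of four therefore belongs to the protocol's own planning scale.

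**5. What complete case can show.** Assume observed counts for grades 0 to 5 of 2/1/2/5/16/41 (rnTMS) and 3/2/3/7/19/33 (sham). A proportional-odds fit gives OR 0.61 (0.32 to 1.18). Adding 4 rnTMS and 1 sham deaths at grade 0 gives 0.74 (0.39 to 1.40). If the complete-case set leaves deaths out, the two analyses disagree, and the disagreement shows how much the deaths matter.

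**The case against.** The strongest reply is that this is detail for the analysis plan. The list of sensitivity analyses is introduced as open, and a detailed SAP is announced. That lowers the weight of the point but does not remove it: the article itself chooses the checks, and the one that bears on missing data says nothing about the assumption most in doubt.

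The second reply is that the primary analysis already handles the main threat by singly imputing deaths and recognised informative dropouts. This stands. A reader might infer that the primary analysis is plain MAR; it is not. The gap concerns only scores that the sorting leaves in the MAR pool.

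A reader might also infer that both sensitivity analyses discard deaths. The article does not say so. The death rule is not tied to one analysis, so a patient scored at the worst value could count as complete, and the per-protocol set is undefined.

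Third, the equivalence in step 2 needs matching covariates, and the article does not specify the imputation model. BMRC is also measured at T1 and T2, which could help. In a linear-model check with assumed correlations, adding T2 reduced the bias from 0.067 to 0.051, about a quarter, so most of it remained.

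Fourth, the harm needs losses that differ between arms and are wrongly classed as MAR. Patients and assessors are blinded, and the article does not predict differential dropout. This also stands and limits the size of the point.

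**Conclusion.** The point holds in a limited form. Neither sensitivity analysis named for motor status tests departures from MAR for missing T3 scores not classed as informative, and agreement between complete case and MAR imputation would not be evidence of robustness for them. It would be too strong to say that the named analyses cannot reveal any dependence on dropouts: comparing the primary result with complete case can expose dependence on the singly imputed values, as step 5 shows.

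At the planned 10% dropout, four adverse rnTMS dropouts out of 7 to 8 are enough to cross 1.35 on the protocol's scale. At the expected 2%, only an extreme split does so.

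A reader might go on to infer a large rise in false non-inferiority claims. The article does not support that as a prediction. In a simulation at the margin with an assumed BMRC distribution and 10% loss, the rate rose from about 2.5% to about 6% when lost rnTMS patients were about four times likelier to be at BMRC 3 or below, and to about 14% when all were. There was almost no rise when both arms lost the same kind of patient, and the rate was at most about 3.5% at 2% missing. Those figures assume that every such patient is left in the MAR pool. The change is worth making because it is cheap and motor status gates the second hypothesis.

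**What to change.** In section {20b}, add a delta-adjusted (tipping-point) analysis of motor status on the 30 imputed data sets already planned. Shift the imputed BMRC scores of missing rnTMS patients who did not die towards worse in steps, leave sham at MAR, and report the shift at which the upper limit of the odds ratio reaches 1.35. State that deaths keep the worst BMRC score in the sensitivity analyses. Keep complete case as a descriptive supplement.

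The cost is a sentence or two in the plan and a few lines of code, with no new data. The downside is that the report may have to say that the non-inferiority claim depends on a few dropouts.
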